#### Recruitment Strategy

Physicians and HCPs will be contacted directly. Potential participants will get a written invitation to participate in the study, including background information for physicians and other HCPs as well as a declaration of participation and agreement. The written approval for participation in the study is included in the informed consent document. The potential participants will send their declaration and participation agreement by mail to GP-HSR. All clinicians at the NCT using the PEPA will receive training demonstrating how to deal with this new instrument.

All patients matching the inclusion criteria will be contacted by their responsible physician at the NCT and asked to participate in the study. The responsible physician will inform them about aims, content, privacy issues, and risks related to the study. After patients give their consent to participate in the study, they will receive a pseudonym. Subsequently, patients will be invited to come to the GP-HSR and receive comprehensive training for handling the PEPA. This training includes a complete introduction to the functionalities of and consequences of working with the PEPA (eg, data security issues, allocating access authorizations). Then the PEPA will be set up individually for every patient, including the transfer of existing PHI (eg, former findings) to the PEPA (via PDF upload).

On the basis of the care setting of the intervention, the general practitioners (and their medical assistants) will be recruited depending on the selected patients. The corresponding general practitioners of the selected patients will be contacted and asked to participate in the study by GP-HSR. With an existing interest, the potential participants will get a written invitation to participate in the study, including background information for physicians and other HCPs as well as a declaration of participation and agreement. Causes for nonparticipation will be documented by GP-HSR. The informed consent document contains the request to give their written approval for participation in the study. The potential participants will send their declaration and participation agreement by mail back to GP-HSR. All participating general practitioners and their medical assistants will receive PEPA training.

#### Inclusion and Exclusion Criteria

Patients must have a diagnosis of colorectal cancer to be eligible for participation (ICD-10: C18, C19, C20). Furthermore, they should be receiving either chemotherapy with curative approach at the NCT after their primary surgery (at least for the next 2 months) or chemotherapy after relapse with symptom-relieving approach at the NCT. The participants must be 18 years of age or older and their disease status has to be classified as UICC stage III-IV.

To be eligible for participation in the study, the clinicians and other HCPs of the NCT as well as general practitioners and their medical assistants have to cooperate closely with the included patients during their treatment at the NCT. Prerequisite for inclusion of patients and professionals in analysis of processes and organizational change is participation within the before and after trial.

All participants who do not meet the inclusion criteria will be excluded. Additional exclusion criteria for patients are severe acute psychiatric disorders (eg, schizophrenia, schizotypal and delusional disorders); dementia; mental and behavioral disorders due to psychoactive substance use; insurmountable language and communication problems; and emergent cases.

#### Data Collection

Data will be collected from patient survey responses and shall be obtained for all patients. Additionally, a sociodemographic questionnaire will help to gain information on age, sex, diagnoses, and educational level. Patients will receive a paper-based outcomes survey questionnaire right before the intervention starts (baseline) and at the end of the 3-month test period. The completion of each questionnaire will take about 45 minutes. All data will be pseudonymized. The collected data will be entered into a database and stored on a secured server.

The basis for conducting interviews will be a semistructured and pilot-tested interview guide. Each interview will be conducted until no newer aspects will be addressed. The interviews will be performed by a trained researcher (the moderator). All interviews will be audio- and videotaped and transcribed verbatim. Videotapes will be used to assist with the transcription of group data. Additionally, sociodemographic data will be collected anonymously using a study-specific questionnaire.

The health economic evaluation focuses on patients and their health services utilization. All consumed goods and services will be assessed from the societal perspective. This perspective assures that all relevant cost categories are included. Service utilization and intervention-related costs are measured by an adopted version of the “Mannheimer Module Resource Consumption” questionnaire. The consumed resources are weighted by standardized unit costs to derive direct and indirect costs.

#### Data Analysis

Because of the exploratory nature of the trial, the primary outcome “self-efficacy”—captured by the CBI-B-G [18]—will be evaluated descriptively at time points T0 and T1, by tabulating the respective means, SDs, medians, first and third quartiles, and minimum and maximum. Furthermore, descriptive *t* tests for paired samples will be applied to investigate potential differences between time points T0 and T1 and descriptive *P* values and 95% confidence intervals will be given. Missing values for the primary outcome at T1 will be replaced by multiple imputation [24] taking the baseline value (T0) into account. Best- and worst-case imputation will be conducted as sensitivity analyses. As in the case of the primary outcome, all secondary outcomes (see Table 1) will be analyzed descriptively by tabulating the measures of the empirical distributions. For continuous outcomes, means, SDs, medians, first and third quartiles, and minimum and maximum will be provided. For categorical outcomes, absolute and relative frequencies will be reported.

For health economic evaluation, descriptive analysis of the excess costs related to the participating patients will be scrutinized. Standard measures of central tendencies and dispersions are selected. This type of cost-of-illness study yields empirical insights into costs and cost components of the PEPA under real-world conditions.

In terms of process evaluation and organizational change, the transcribed texts of all interviews will be the basis for performing the qualitative content analysis. Data will be taken from the transcribed texts, edited, and analyzed [25]. This will be done by using a preliminary category system (search grid), which is based on themes and questions of the interview guide. In addition, the category system will be continuously adapted during the analysis process. For data analysis, in a first step, 2 out of all transcriptions will be analyzed independently by 3 members of the research team to identify relevant key issues. Following that, the key findings will be discussed within the research team and the preliminary category system will be adapted. Afterward, all key issues will be labeled as codes and these codes will be organized into main categories and subcategories. Each code will be clearly defined and linked with samples from the transcriptions. Labeling categories will be performed by using ATLAS.ti version 7.0.80 (Scientific Software Development GmbH).

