#### Objectives

##### Outcome Evaluation

The primary objective of this study is to assess patients’ self-efficacy, among all participants, using the German version of the Cancer Behavior Inventory–Brief Version (CBI-B-G). CBI-B-G has high internal consistency (Cronbach alpha=.85) and correlates substantially with generalized self-efficacy (*r*=.57, *P*<.001) and emotional functioning (*r*=.53, *P*<.001) [18].

CBI-B-G scores are assessed at baseline (T0) and after 12 weeks of PEPA usage (T1). We will determine whether there is a difference in CBI-B-G scores after using the PEPA prototype for 3 months (T1) compared with baseline (T0). Furthermore, a number of secondary outcomes will be measured (see Table 1).

**Table 1 table1:** Overview of outcome parameters and measurement instruments in this study.

Outcome parameters	Measurement instruments	Items
Patient self-efficacy (primary outcome)	German version of the Cancer Behavior Inventory–Brief Version (CBI-B-G) [18]	14
Control preferences	Control Preferences Scale [19]	5
Psychosocial distress	Distress Thermometer [20]	1
Utilization of medical services	[Mannheimer Module Resource Consumption]^a^	30
Involvement in care	Perceived Involvement in Care Scale [21]	13
Usability of PEPA^b^ prototype	System Usability Scale [15]	10

^a^Not published.

^b^PEPA: personal electronic health record.

In terms of health economic evaluation, it has been hypothesized that PHRs increase the virtual access to care and reduce health care costs [22,23]. The objective of this health economic work package is to collect data likely to support or reject these assumptions. This includes the following:

to collect data on service utilization and unit cost of treatments or service contacts in order to assess direct medical costs of study subjects 3 months before the intervention and during the PEPA-intervention phaseto collect data on work absentees and productivity loss 3 months before the intervention and during the PEPA-intervention phase to estimate indirect costs of study subjectsto identify potential factors and PEPA-related effects likely to influence health care costs from the health system and societal perspective

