#### Sample Size

For the planned before and after trial, the sample size of up to 30 patients is solely based on matters of feasibility (due to the exploratory nature of the trial). With this number of patients, a standardized treatment effect of 0.53 can be demonstrated with a power of 1−β=0.8 at a (descriptive) two-sided significance level of alpha=.05 by applying a paired-sample *t* test. Additionally, we will conduct interviews with all participating patients and professionals.

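### The T0 score is the only predictor named for imputing missing T1 self-efficacy; treatment intent should be named as well

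*Protocol article*

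**What the plan says.** All references are to the protocol article, Phase 2: Implementation Study.

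- **Data Analysis.** Paired T0-T1 comparison of the CBI-B-G score with descriptive P values and 95% confidence intervals. On missing data: "Missing values for the primary outcome at T1 will be replaced by multiple imputation [24] taking the baseline value (T0) into account". No other predictor is named, and none is ruled out. As sensitivity analyses, missing scores are also filled in under a best case and a worst case.
- **Inclusion and Exclusion Criteria.** Two groups may enter, both UICC stage III-IV: patients on curative chemotherapy after primary surgery, and patients on "chemotherapy after relapse with symptom-relieving approach at the NCT".
- **Data Collection.** The paper outcomes survey is given at baseline and at the end of the 3 months, so the Distress Thermometer (Table 1) appears to be available at T0. In addition, "a sociodemographic questionnaire will help to gain information on age, sex, diagnoses, and educational level". Treatment intent is not in that list, but it must be known to apply the entry criteria.
- **Sample Size.** "the sample size of up to 30 patients is solely based on matters of feasibility". No allowance for dropout is stated.

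**The concern.** An imputation model with T0 as its sole predictor assumes that, among patients with the same baseline self-efficacy, failure to return the T1 questionnaire is unrelated to anything else that bears on T1. The entry criteria make that doubtful. A patient on symptom-relieving treatment after relapse is plausibly less likely to complete a 45-minute questionnaire at 3 months than one on curative treatment after surgery, and may also change differently over that time. Such a patient would be filled in from responders with the same T0 score, most of them drawn from the group that stays.

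At stake is the primary result. The mean change and its confidence interval are meant to describe all enrolled patients, but would be pulled toward those who remained well enough to answer.

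**Working it through.** **1. The plan's own figure.** Inputs from Sample Size: n = 30, "a standardized treatment effect of 0.53 can be demonstrated", "power of 1−β=0.8", "two-sided significance level of alpha=.05", paired t test. With the noncentral t distribution (df = 29, noncentrality 0.53 × √30), power is 0.801 and the effect detectable at 80% power is 0.529. The statement is correct and does not depend on the imputation model.

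**2. What T0-only imputation estimates.** If T0 has the same distribution in both intent groups, and loss depends on intent only, the regression of T1 on T0 among responders gives the missing patients the responders' average change. The overall estimate is then the completers' mean. With an even mix of intents:

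- truth = 0.5 μ_cur + 0.5 μ_sym
- T0-only estimate = w μ_cur + (1 − w) μ_sym, where w = (1 − m_cur) / [(1 − m_cur) + (1 − m_sym)] and m is the proportion missing at T1
- bias = (w − 0.5) × (μ_cur − μ_sym)

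**3. Numbers.** The mix, the dropout rates and the difference in change are assumptions; none is in the documents. The unit is one SD of change.

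| Missing, curative / symptom-relieving | w | Bias, difference 0.5 SD | Bias, difference 1.0 SD |
|---|---|---|---|
| 10% / 25% | 0.90/1.65 = 0.545 | 0.023 | 0.045 |
| 5% / 25% | 0.95/1.70 = 0.559 | 0.029 | 0.059 |
| 10% / 30% | 0.90/1.60 = 0.563 | 0.031 | 0.063 |
| 10% / 40% | 0.90/1.50 = 0.600 | 0.050 | 0.100 |
| 5% / 40% | 0.95/1.55 = 0.613 | 0.056 | 0.113 |
| equal | 0.500 | 0 | 0 |

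The standard error at n = 30 is 1/√30 = 0.183. The bias therefore runs from 0.023/0.183 = 12% to 0.113/0.183 = 62% of a standard error. If there is no difference in change, it is zero at any dropout.

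**4. Check by simulation.** Large-sample runs (400,000 patients per scenario) used a true mean change of 0.53 SD, 30% or 50% symptom-relieving patients, a T0-T1 correlation of 0.6, and T0 equal or 0.5 SD lower in the symptom-relieving group. Dropout was 10/30%, 10/40%, 5/30% or 20/20%, and the difference in change 0.5 or 1.0 SD.

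- With unequal dropout, T0-only imputation gave 0.56 to 0.65, a bias of about 0.03 to 0.12 SD (0.14 to 0.64 of the standard error).
- It equalled the completers' mean when T0 did not differ by intent. Otherwise it lay 0.01 to 0.02 SD further from the truth than that mean.
- With 20/20% dropout the bias was zero.
- Adding treatment intent returned 0.53 in every scenario.

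**5. Patients available to fit the model.** With 15 patients per group, observed T1 values number 15 × (0.90 + 0.60) = 22.5 to 15 × (0.95 + 0.75) = 25.5. Of these, 15 × 0.60 = 9 to 15 × 0.75 = 11.25 are symptom-relieving.

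**6. Width of the extreme-case bounds.** As an illustration, take 6 of 30 missing and extremes 2 to 3 SD of change from the mean. The estimate then moves by 6/30 × 2 = 0.4 to 6/30 × 3 = 0.6 SD in each direction, about as much as the whole detectable effect of 0.53.

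**The case against.** A reader might infer that the plan fixes imputation on T0 and nothing else. The sentence does not say so: T0 is to be taken into account, and no variable is excluded. A condensed article may leave the full covariate list to an analysis plan that is not shown. This stands as a limit on the wording. It does not remove the point, because the article specifies the method, names one predictor and stops there; an analyst following it would use T0.

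A reader might also infer that the plan ignores informative loss, or that better predictors than T0 are already in hand. Neither is supported. Best- and worst-case imputations are planned and do bracket such loss, although bounds as wide as those illustrated cannot show a shift of about 0.1 SD and leave the primary estimate unchanged. Nothing in the documents shows that any variable predicts T1 better than T0; intent and distress are additional predictors, and intent is not among the listed questionnaire items.

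Three further objections stand:

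- The harm is wholly conditional. The 0.183 standard error also counts 30 observed changes. At 5%/40% missing, about 23 are observed, the standard error is 1/√23.25 = 0.207, and the largest bias is 0.113/0.207 = 54% of it. Even a shift of 0.62 standard errors would lower 95% coverage only to about 90%.
- With 22 to 26 observed T1 values, and possibly fewer because 30 is an upper limit, a sparse model is defensible.
- The trial is exploratory, its P values are descriptive, and the article disclaims causal conclusions. No confirmatory decision depends on this.

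**Conclusion.** The concern holds in a limited form. T0 is the only predictor named for a sample that deliberately mixes two prognostically different groups. If dropout and change both differ by treatment intent, the T0-only analysis offers essentially no protection beyond a completers' analysis. Under the stated assumptions the bias is about 0.02-0.11 SD, roughly 12-62% of the standard error at n = 30, toward the group that stays. With equal dropout or equal change it is zero.

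The documents supply none of the inputs that decide between these cases, so it cannot be said that the confidence interval will be centred on a wrong value, only that it could be. Nor would baseline predictors repair all loss due to the course of the disease; they remove only the part they explain. This is a modest, inexpensive improvement to the primary analysis. It is not a flaw in the design or in the sample size statement.

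**What to change.** In Phase 2, Data Analysis:

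- State that the imputation model for T1 CBI-B-G includes the T0 CBI-B-G score and treatment intent (curative or symptom-relieving), taken from the eligibility check and carried into the study database.
- Add the T0 Distress Thermometer if the number of observed T1 values allows.
- Report the number of missing T1 scores by treatment intent.
- Keep the T0-only model and the best- and worst-case imputations as sensitivity analyses.

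The cost is a change of wording and one extra database field, with no new patient assessment. The downsides are a slightly less stable imputation model on about 22-26 observed T1 values and no correction for loss driven by progression after T0, which the report should say.

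### Missing T1 self-efficacy scores: T0 is the only imputation predictor named and the only checks are extreme fills, so there is no graded test for illness-related dropout

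*Protocol article*

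**What the plan says.** The primary outcome is the CBI-B-G score, measured only at baseline (T0) and after 12 weeks (T1) in a single group. Under Phase 2, *Sample Size*, "the sample size of up to 30 patients is solely based on matters of feasibility", with this reading of what the number buys: "With this number of patients, a standardized treatment effect of 0.53 can be demonstrated" "with a power of 1−β=0.8". No dropout rate is given.

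Under Phase 2, *Data Analysis*, descriptive t "tests for paired samples will be applied to investigate potential differences between time points T0 and T1", with 95% confidence intervals. Missing T1 values are multiply imputed "taking the baseline value (T0) into account". Then: "Best- and worst-case imputation will be conducted as sensitivity analyses". The section does not say whether best and worst mean the limits of the scale or the extremes observed.

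Under Phase 2, *Inclusion and Exclusion Criteria*, all patients have stage III-IV disease. They receive either curative chemotherapy after surgery or "chemotherapy after relapse with symptom-relieving approach at the NCT". Treatment intent is therefore known at entry. Table 1 lists the Distress Thermometer, a single item, among the outcomes surveyed.

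**The concern.** The two treatment groups differ in prognosis, and T1 depends on returning a long paper questionnaire at three months. It is plausible that the sicker patients return it less often and that their self-efficacy falls more. An imputation model that knows only T0 fills their T1 as if they had changed like the patients who returned the form, and the mean change then looks better than it was.

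A sensitivity analysis should show how far the missing patients would have to differ before the conclusion changes. Two extreme fills give only the ends of the range. The main outputs here are a mean change and its confidence interval, so it matters whether a reader can judge how much dropout moved them.

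**Working it through.** **Inputs from the protocol article:** up to 30 patients, standardized effect 0.53, power 0.8, two-sided 0.05, paired t test.

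**Assumptions (not in the document):** share on symptom-relieving treatment 30-60%; T1 missing in 30-40% of these and 5-10% of curative patients; difference in mean change between the groups 0.5-0.8 SD of change; T0-T1 correlation r = 0.5-0.7; scale limits k = 2-3 baseline SDs from the T0 mean.

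**1. The plan's own figure.** Noncentral t with 29 df and noncentrality 0.53 × √30 = 2.90 gives power 0.801. The stated 0.53 reproduces.

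**2. Bias from leaving out treatment intent.** Let π be the symptom-relieving share, m_P and m_C the missing rates in the two groups, and g the difference in mean change. If T0 carries no information on intent,

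bias = g × (π − π_obs), with π_obs = π(1−m_P) / [π(1−m_P) + (1−π)(1−m_C)].

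| | π | m_P | m_C | g | π_obs | bias |
|---|---|---|---|---|---|---|
| Low corner | 0.30 | 0.30 | 0.10 | 0.5 | 0.21/0.84 = 0.250 | 0.025 |
| High corner | 0.60 | 0.40 | 0.05 | 0.8 | 0.36/0.74 = 0.486 | 0.091 |

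The standard error of the mean change with 30 complete pairs is 1/√30 = 0.18 SD, so the bias is at most about half a standard error.

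**3. Bias if dropout depends on the unseen T1 score.** This was simulated with imputation from T0 and log-odds of dropout of 0.5 to 2 per SD of T1. Bias is in SD of change.

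| Missing | Dropout depends on T0 only | Dropout depends on T1 |
|---|---|---|
| 10% | 0.00 | +0.03 to +0.11 |
| 20% | 0.00 | +0.06 to +0.21 |
| 30% | 0.00 | +0.10 to +0.30 |

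**4. Reach of the worst-case fill at the scale limit.** In baseline SDs, a true change of 0.53 SD of change equals e = 0.53 × √(2(1−r)), which is 0.53 at r = 0.5 and 0.41 at r = 0.7.

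- Missing share that brings the estimate to zero, p = e/(e+k): from 0.41/3.41 = 12% to 0.53/2.53 = 21%, or about 4 to 6 of 30 patients.
- Shift at 20% missing, 0.2(k+e)/√(2(1−r)): from 0.2 × 2.53/1 = 0.51 to 0.2 × 3.41/0.775 = 0.88 SD of change.
- Best-to-worst span at 20% missing with symmetric limits, 0.2 × 2k/√(2(1−r)): from 0.8 to 1.5 SD of change.

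**5. Chance that a significant complete-pair result stays significant after the worst-case fill.** Simulated with n = 30 and dropout at random, with fills at the scale limit or at the observed extreme.

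| Missing T1 | True effect 0.53 | True effect 1.0 |
|---|---|---|
| 0 | 100% | 100% |
| 1 | 41-80% | 96-100% |
| 3 | 1-43% | 24-95% |
| 6 | 0-14% | 0-69% |

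With 6 missing and a true effect of 0.53, the best-case fill turns 93-99% of non-significant results significant. At that level of loss the two fills nearly always disagree about significance.

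**6. A graded shift for comparison.** Lowering the imputed T1 values by 1 baseline SD at 20% missing moves the estimate by 0.2 × 1/√(2(1−r)) = 0.20 to 0.26 SD of change. The steps from 0 to 1 SD therefore cover most of the bias range found at 20% missing in step 3, which the extreme fills overshoot.

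**The case against.** The strongest reply has four parts.

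- **The predictor list may be longer.** A reader might infer that T0 is the only variable allowed in the model. The text says that T0 is taken into account; it does not exclude others, and an article may leave the full list to a document not shown. This stands as a limit on the wording: T0 is the only predictor *named*.
- **Bias is not established.** A reader might infer that the main estimate is biased. It is unbiased if dropout depends on T0 only, and no dropout rate or mechanism is given. The loss from omitting intent is also small beside the standard error. Both stand. Added predictors would only partly address dropout that depends on T1 itself.
- **Extreme fills are legitimate.** They bound non-ignorable dropout without a dropout model. A reader might infer that the worst case overturns any result whatever the data show. That is wrong: with no missing T1 nothing changes, and with one missing many results survive. What remains is that the bounds lose their use at about 20% missing and that the fill values are undefined.
- **Deaths.** A reader might infer that the plan means to impute scores for patients who died. The document has no rule on deaths; it simply makes no exception for them.

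The reply does not remove the point. The article states a specific method and specific checks, and a better alternative exists with data already collected.

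**Conclusion.** The point holds as a cheap improvement, not as an error in the plan. With T0 the only named predictor and two undefined extremes the only checks, the stated analysis cannot show how sensitive the T0-T1 change is to moderate illness-related dropout. If patients on symptom-relieving treatment are lost more often and decline more, the estimate is too favourable by about 0.03-0.09 SD. It could be out by up to about 0.3 SD at 30% missing if loss depends strongly on the unseen score. At 6 of 30 missing, the worst case alone moves the estimate by about as much as the 0.53 effect, or more.

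Every one of these sizes rests on the assumed missing rates, group difference, correlation and scale limits. The severity is minor, because P values and intervals are descriptive and the limitations section presents the outcome evaluation as exploratory.

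**What to change.** 1. Impute T1 CBI-B-G from T0 CBI-B-G, treatment intent (curative or symptom-relieving) and the T0 Distress Thermometer.
2. Make a delta-adjusted multiple imputation the main sensitivity analysis. Lower the imputed T1 values in steps from 0 to 1 SD, name the SD used, and report the step at which the conclusion changes, if any.
3. Show the complete-pair result beside it.
4. Keep best- and worst-case fills as supplementary outer bounds, and define the fill values.
5. Report deaths before T1 separately and do not impute a score for them.

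No new data are needed. The cost is a change to the analysis text and a few lines of code, plus two more predictors in an imputation model fitted to at most 30 patients.
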